### Statistical analysis

The RMT and MEP statistical analysis will be performed using the Statistical Package for Social Science (SPSS) version 17.0 (SPSS Inc., Chicago, IL, USA). Levene’s test for homogeneity of variance will be applied. If measurement data are normally distributed then the independent *t* test will be used to analyze between-group differences for each subject before and after electro-acupuncture or sham electro-acupuncture, and between the electro-acupuncture group and the sham electro-acupuncture group. Otherwise, the Wilcoxon rank sum test for a nonparametric distribution will be used. A *p* value less than or equal to 0.05 will be considered statistically significant.

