### Sham electro-acupuncture

For sham electro-acupuncture, the K Streitberger placebo needle (Huatuo, Suzhou Medical Supply Factory Co. Ltd., Suzhou, China) will be applied at CV 23 and GV 16. The K Streitberger placebo was invented by Streitberger in 1998, which is a validated and reliable single-blind acupuncture needle used to investigate the effects of acupuncture [24]. This single-blind placebo needle is widely used in acupuncture research. The HANS acupuncture point nerve stimulator will be connected to the placebo. The RMT and MEP of the mylohyoid will be measured before and after electro-acupuncture or sham electro-acupuncture. Previous studies have reported using TMS to study the cortical topography of the human swallowing musculature in healthy subjects by recording RMT and MEP [14].

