### Sample size calculation

The sample size was calculated based on a pretest from a reference in this field, where the sample size was 19.36 and calculated according to the statistical formula: $$ n=\frac{2\left[{\left(\upalpha +\upbeta \right)}^2{\sigma}^2\right]}{{\left({\upmu}_1-{\upmu}_2\right)}^2} $$ where *n* was the sample size of the treatment group/control group, α is the significance level, β is the power of the test, σ is the population variance (SD) and μ_1_ − μ_2_ is the smallest effect of interest. In this study, α = 0.05, β = 0.80 (80%), σ was estimated at 13.07, and μ_1_ − μ_2_ was the RMT of the swallowing-related muscle groups (the most important index to evaluate lateralization of the human swallowing motor cortex excitability). This was the minimum clinical significance value for the RMT of the swallowing muscles that was calculated from previous trials and expert assessments, based on the primary clinical data, which was estimated at 3.57 ([name]. Effect of Electro-acupuncture at Acupoints on the Swallowing Motor Cortex in Humans, unpublished). Therefore, a sample size of 19.36 is needed in each group (electro-acupuncture and sham acupuncture). We will include 20 subjects per group condition.

Forty healthy subjects will be randomized 1:1 to the electro-acupuncture or the sham electro-acupuncture groups. Both groups will receive TMS (Magstim 200, Magstim Co. Ltd., Whitland, Wales, UK). The RMT and the MEP of the mylohyoid will be recorded using EMG (Nicolet Viking Quest, Wisconsin, USA) before and after one 15-min electro-acupuncture or sham electro-acupuncture treatment. The whole study procedure from assessing eligibility to completion of the treatment will last between 1 and 2 h.

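### The plan names an unpaired test for before-after comparisons within the same subjects; this loses power there but leaves the randomized comparison intact

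*Protocol article*

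**What the plan says.** The Statistical analysis section gives one rule for RMT and MEP. For normally distributed data it names the independent t test and gives it two uses. The first is described in these words: "test will be used to analyze between-group differences for each subject before and after electro-acupuncture or sham electro-acupuncture". The second, listed as a separate item, is the arm comparison: "and between the electro-acupuncture group and the sham electro-acupuncture group". For data that are not normal, the rule is: "Otherwise, the Wilcoxon rank sum test for a nonparametric distribution will be used". The threshold is a p "value less than or equal to 0.05 will be considered statistically significant"; sidedness is not stated. Neither a paired t test nor a signed-rank test is named anywhere in the article.

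The design is before-after within each subject. The section on sham electro-acupuncture states: "The RMT and MEP of the mylohyoid will be measured before and after electro-acupuncture or sham electro-acupuncture". The last paragraph under Sample size calculation confirms that both recordings bracket a single 15-minute session.

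The primary outcome (Outcome measures) is the percent change in RMT. The Background states the hypothesis as a fall in RMT and a rise in MEP amplitude after electro-acupuncture.

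**The concern.** The independent t test and the rank sum test both assume that the two sets of values come from different, independent subjects. Here each after-value belongs to the same person as a before-value, and the two are likely to be positively correlated. The unpaired standard error leaves that correlation out and is therefore too large.

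What is at stake is the within-group before-after result. The Background words its hypothesis as such a change and says that seeing it will show activation of the swallowing motor cortex. A modest real change could be reported as no change because of the test chosen, and the p values would not have their nominal meaning.

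**Working it through.** **Inputs from the article (Sample size calculation, Statistical analysis).** Planning values: "α = 0.05, β = 0.80 (80%), σ was estimated at 13.07"; the difference, "which was estimated at 3.57"; and "We will include 20 subjects per group condition", which gives 20 before-after pairs for each within-group test.

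**Assumptions.** The test is two-sided at 0.05. The SD of 13.07 applies to a single measurement at both times. The before-after correlation ρ is not in the article, so a range is shown. The value 3.57 was set for treatment versus control; it is borrowed here as an illustrative within-group change.

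**Reproducing the plan's own figure.** Putting 0.05 and 0.80 directly into the printed formula gives 2 × (0.05 + 0.80)² × 13.07² / 3.57² = 19.37, against the stated 19.36. So 13.07 was squared, that is, used as an SD. (That this formula takes α and power where normal quantiles belong is a separate matter.)

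**Standard errors of the mean change, n = 20.**
- Unpaired: 13.07 × √(2/20) = 4.13, whatever ρ is.
- Paired: 13.07 × √(2(1 − ρ)/20), which is 3.46, 2.92, 1.85 and 1.31 at ρ = 0.3, 0.5, 0.8 and 0.9.
- Ratio: 1/√(1 − ρ), that is 1.20, 1.41, 2.24 and 3.16.

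**Observed mean change needed for p ≤ 0.05, with the SD at its planned value.**
- Unpaired, 38 degrees of freedom: 2.024 × 4.133 = 8.37, which is 8.37 / 3.57 = 2.3 times the planned difference.
- Paired, 19 degrees of freedom (critical value 2.093): 7.24, 6.12, 3.87 and 2.74 at the same four values of ρ.

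**Power at a true change of 3.57, and type I error.** Paired power is from the noncentral t distribution. Unpaired figures are from simulated correlated normal pairs (at least 100,000 data sets per setting).

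| ρ (assumed) | Unpaired power | Paired power | Unpaired type I error |
|---|---|---|---|
| 0 | 13% | 13% | 5% |
| 0.3 | 9% | 17% | 2% |
| 0.5 | 6.5% | 21% | 0.7% |
| 0.8 | 1.6% | 45% | below 0.1% |
| 0.9 | 0.5% | 74% | about 0 |

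**Fallback tests.** Rank sum against signed-rank (4,000 data sets per setting) shows the same pattern: about 6% against 19% at ρ = 0.5, 2% against 42% at 0.8, and 0.7% against 71% at 0.9.

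**Larger true changes, unpaired test, ρ from 0.5 to 0.9.** At a change of 7 the power is 34% falling to 25%. At a change of 10 it is 71% rising to 83%.

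**The case against.** **The wording can be read differently.** Differences between groups for each subject before and after could mean each subject's change, compared between arms, where an independent test is right. That reading is possible. But the arm comparison then follows as its own item, so this reading would make the first item a duplicate of the second. The within-subject reading is more natural, and on either reading the sentence needs rewriting.

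**The main comparison is sound.** This stands in full. A reader might infer that the trial's conclusion about electro-acupuncture versus sham is compromised. The article does not support that: percent change in RMT already reduces a subject's two readings to one number, and an independent test between randomized arms suits it.

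**The error is conservative.** This also stands. With positive correlation the type I error falls below 5%, so this choice cannot by itself create a false claim of an effect. Nor does the section plan any confidence intervals that would be wrong.

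**The size depends on assumptions.** A reader might infer that the within-group test can hardly ever reach significance. That is too strong, because ρ is unknown, 3.57 is only the smallest difference the sponsor cares about, and a change of about 10 would usually be found. At ρ = 0.5 even the paired test reaches only 21%, so part of the weakness is 20 subjects per group. The article also labels σ as both a variance and an SD. If 13.07 were a variance (SD 3.62), the unpaired test would have 86% to 99% power at 3.57 for ρ from 0 to 0.9. The sample size arithmetic squares 13.07, so the SD reading is the likelier one.

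**Left-right comparisons.** A reader might extend the point to the two hemispheres. The section specifies no left-right test, so no wrong test has been fixed there.

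**Conclusion.** The point holds in a limited form: the rule is wrong as written. On its natural reading, it fixes an unpaired test, with an unpaired fallback, for paired before-after data. This is a stated choice, not a detail left to an analysis plan.

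The consequence is lost power in the within-group results, growing with ρ from a modest loss at 0.3 to a severe one at 0.8 and above for a change of the planned size. These figures rest on an assumed ρ, on 13.07 being the SD of a single measurement, and on 3.57 standing in for the within-group change. The direction of the error needs only positive correlation. The randomized comparison of percent change in RMT is not affected.

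**What to change.** Rewrite the sentence in Statistical analysis so that it separates the two comparisons:
- **Before versus after, within subjects:** paired t test, with the Wilcoxon signed-rank test as fallback and normality checked on the differences.
- **Electro-acupuncture versus sham:** keep the independent t test, or the rank sum test, applied to each subject's change.

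State that the within-group tests are descriptive and that the conclusion about electro-acupuncture rests on the between-arm comparison. The declared primary outcome need not change. The cost is a sentence or two of text, with no new data and no change to study conduct.

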**Discussion:**

The aim of this trial is to explore whether lateralization of the human swallowing motor cortex excitability in healthy subjects is present, and to determine if electro-acupuncture to acupuncture points Lianquan (CV 23) and Fengfu (GV 16) will exert an effect on it under normal physiological conditions.

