Plasticity of the swallowing motor cortex is imperative for the recovery of patients with OD after stroke. It requires stimulation from sensory input and an undamaged map area. Studies examining the mechanisms of electro-acupuncture on OD as a sequela of stroke are difficult to perform. Therefore, lateralization of the human swallowing motor cortex excitability with electro-acupuncture in healthy subjects must be performed. The aim of this trial is to explore whether lateralization of the human swallowing motor cortex excitability in healthy subjects is present. We will then investigate the effects of electro-acupuncture on lateralization of the human swallowing motor cortex excitability by recording the resting motor threshold (RMT) and the motor evoked potential (MEP) changes in an electro-acupuncture and a sham electro-acupuncture group. We hypothesize that after administering electro-acupuncture to healthy subjects there will be a decrease in the RMT and an increase in the amplitude of the MEP in the swallowing motor cortex. This will demonstrate the activation of the swallowing motor cortex by electro-acupuncture. Results of this study will both help identify the swallowing mechanism in healthy subjects and enhance the understanding of the pathological mechanisms of OD as a sequela of stroke. It is possible the other undamaged hemisphere map area may be activated by electro-acupuncture as well, which may ultimately demonstrate mechanisms of cerebral functional reorganization and cerebral plasticity in OD as a sequela of stroke.

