## Methods/design

### Study design

This will be a single-blind, randomized controlled trial (RCT). Electro-acupuncture will be compared with sham electro-acupuncture to determine if electro-acupuncture has an effect on lateralization of the human swallowing motor cortex excitability. Forty healthy subjects will be blinded to the study condition. This RCT will be conducted at the South China Research Center for Acupuncture and Moxibustion from April 2017 to April 2019. This trial has been registered with the Chinese Clinical Trial Registry (ChiCTR-IOR-17011359). The study design is presented in the flowchart in Fig. 1. The Standard Protocol Items: Recommendations for Interventional Trials (SPIRIT) checklist is provided as Additional file 1.

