### Outcome measures

#### Primary outcome measure

TMS has been widely used for assessing cortical excitability. At the same time, the RMT, as a TMS measure, can be used as an indicator of cortical excitability, which is reliable in single pulse TMS measures [25, 26]. Thus, the primary outcome measure will be the percent change in the RMT of the mylohyoid at baseline and after the electro-acupuncture or sham electro-acupuncture treatment. The RMT of the mylohyoid will be delivered by a TMS pulse every 30 s bilaterally to the left and right swallowing motor cortices, respectively, for 10 pulses in the fully relaxed state. The MEP of the mylohyoid should be greater than or equal to 30 μV for at least half, or 5 of the 10 TMS pulses. The RMT is defined as the minimum intensity that is needed to elicit the MEP ≥ 30 μV in at least 50% of pulses.

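### The stated question is lateralization, but neither the primary outcome nor the planned tests include a left-versus-right contrast, so the analysis as written does not answer it

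*Protocol article*

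**What the plan says.** Lateralization is the declared question throughout. The Background says "The aim of this trial is to explore whether lateralization of the human swallowing motor cortex excitability in healthy subjects is present", and the Abstract's discussion repeats that aim. Study design states the second aim: the two arms are compared "to determine if electro-acupuncture has an effect on lateralization of the human swallowing motor cortex excitability".

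The Primary outcome measure section says that "the primary outcome measure will be the percent change in the RMT of the mylohyoid", at baseline and after treatment. Pulses are delivered "bilaterally to the left and right swallowing motor cortices, respectively", so each subject yields an RMT for each hemisphere at each time. The section names no side, no left-minus-right difference and no laterality index.

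The Statistical analysis section assigns a two-sample t procedure, or a rank sum test if the data are not normal, to two comparisons. The first is over time, and the wording is: "test will be used to analyze between-group differences for each subject before and after electro-acupuncture or sham electro-acupuncture". The second sets one arm against the other, worded as follows: "and between the electro-acupuncture group and the sham electro-acupuncture group". A p "value less than or equal to 0.05 will be considered statistically significant". Hemisphere is not mentioned there.

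**The concern.** Lateralization is a difference between the two hemispheres of the same person. Showing that it is present needs a within-subject comparison of left with right. Showing that electro-acupuncture changes it needs that left-right difference compared between arms, which is the group-by-hemisphere interaction. A before-after test and an arm-versus-arm test of RMT answer another question: whether excitability moved.

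If electro-acupuncture lowered RMT equally on both sides, the hypothesis at the end of the Background (lower RMT, higher MEP amplitude) would be confirmed with lateralization unchanged. At stake is whether the trial's title question gets a pre-specified answer or one improvised after the data are seen.

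**Working it through.** **1. Aims against tests**

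| Aim | Contrast needed | In the stated analysis? |
|---|---|---|
| Is lateralization present? (Abstract, Background) | Left versus right RMT within subject, at baseline | No |
| Does electro-acupuncture change it? (Study design) | Left-minus-right change, electro-acupuncture versus sham | No |
| Does electro-acupuncture activate the cortex? (hypothesis in Background) | RMT change, electro-acupuncture versus sham | Yes |

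**2. The plan's own figure.** Sample size calculation gives 19.36 per group from SD 13.07 and difference 3.57. The printed formula with 0.05 and 0.80 inserted as plain numbers gives 2 × (0.05 + 0.80)² × 13.07² / 3.57² = 2 × 0.7225 × 170.82 / 12.74 = 19.37, so the figure reproduces. With two-sided normal quantiles it would be 2 × (1.960 + 0.842)² × 170.82 / 12.74 = 210.4, or 211 per group. That is a separate matter. Here it matters that the calculation concerns one RMT difference between two groups, not a left-right contrast.

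**3. The possible ways of handling two sides.** The article does not choose between them.

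*Averaged.* The left-right difference is removed from the data before testing.

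*Tested separately at 0.05, no adjustment.* Familywise error for two independent tests is 1 − 0.95² = 0.0975. For correlated two-sided normal test statistics it is 9.1% at correlation 0.5 and 7.8% at 0.8. The correlations are assumed; the article gives none.

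*Tested separately, with one significant side read as lateralization.* Suppose the effect is identical on both sides, with per-side power p. The probability that exactly one side is significant is 2(p − P(both significant)), which is 2p(1 − p) under independence:

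| Per-side power (assumed) | Correlation 0 | 0.5 | 0.8 |
|---|---|---|---|
| 13.4% | 23% | 17% | 11% |
| 30% | 42% | 29% | 18% |
| 50% | 50% | 33% | 20% |
| 80% | 32% | 23% | 14% |

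The 13.4% row is the two-sided t-test power at 20 per group for difference 3.57 and SD 13.07.

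**4. Precision of the contrast that would answer the question.** Assume SD 13.07 for the analysed RMT quantity on each side, left-right correlation ρ, a true between-group difference of 3.57 in the left-minus-right contrast, and a two-sided test at 0.05. The SD of the contrast is 13.07 × √(2(1 − ρ)).

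| ρ (assumed) | SD of contrast | 3.57 / SD | Power, 20 per group (t test) | n per group for 80% power (normal approximation) |
|---|---|---|---|---|
| 0 | 18.48 | 0.193 | 9% | 421 |
| 0.5 | 13.07 | 0.273 | 13% | 211 |
| 0.7 | 10.12 | 0.353 | 19% | 127 |
| 0.9 | 5.85 | 0.611 | 47% | 43 |

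At ρ = 0.5 the contrast is exactly as precise as a one-side effect, since 2(1 − 0.5) = 1. It is less precise below 0.5 and more precise above.

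**The case against.** Three objections deserve an answer.

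First, a reader might infer that RMT gets two chances at 0.05 and that the investigators will read lateralization from one side being significant and the other not. The article says neither. It records both sides and is silent on whether they are averaged, differenced or tested apart. The error rates in step 3 therefore describe what would follow from separate testing, not what the plan prescribes. This objection stands in full.

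Second, a reader might infer that the trial cannot answer its title question. That is too strong. Both hemispheres are measured before and after treatment in both arms, so the data allow the contrast; the gap is in the stated tests. The first aim is also worded as exploratory, and the electro-acupuncture versus sham comparison does address the activation hypothesis.

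Third, a journal article condenses, and an unseen analysis plan could add the contrast or a multiplicity rule. For multiplicity alone that would be a sufficient reply. It is not sufficient for the main point, because the article does fix a primary outcome and names its comparisons, and what it fixes does not match its aim. A plan that made the left-right contrast the test of that aim would be changing the primary analysis declared here.

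**Conclusion.** The point holds as a mismatch between aim and analysis: carried out exactly as written, the stated tests would not answer either lateralization aim. This rests on the text alone and needs no assumption.

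The numerical consequences are conditional. They apply only if the sides are tested separately, and they depend on correlations and per-side power that the article does not give. Under those assumptions the familywise error would be moderately raised rather than grossly inflated. The larger hazard is mistaking discordant significance for a difference between hemispheres. The documents do not support saying that the article plans separate tests, or that the trial is incapable of addressing lateralization.

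**What to change.** In Statistical analysis and Primary outcome measure:

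1. For the aim that electro-acupuncture changes lateralization, pre-specify the between-group comparison of left-minus-right RMT change. Use either an ANCOVA of the post-treatment left-minus-right difference on its baseline value, or a mixed model with both hemispheres, group, hemisphere, their interaction, baseline RMT and a subject random intercept. The two are close but not identical, so name one.
2. Test the group effect averaged over hemispheres next, in fixed sequence, for the activation hypothesis.
3. For the aim that lateralization is present, compare baseline left with right RMT by a paired test in all 40 subjects.
4. State that this redefines the primary outcome, which is now percent change in RMT.

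No new measurements are needed, but this is more than a wording change: it alters the primary outcome, and the sample size was not derived for this contrast. Power with 20 per group is only about 9% to 47% for ρ from 0 to 0.9 under the assumptions in step 4. With the fixed sequence, the activation test is confirmatory only if the first test succeeds. Report the estimate with its confidence interval, and do not read a non-significant result as absence of an effect on lateralization.

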### Ethical considerations

This study conforms to the principles of the Declaration of Helsinki. The trial protocol has been approved by the China Ethics Committee of Registering Clinical Trials (reference number ChiECRCT-20170038) on 30 June 2017. Signed consent will be obtained from each subject after they are informed of the procedures, possible risks of the study, the allowances, and their right to discontinue participation at any time. If adverse events occur, the subjects will be treated emergently and the China Ethics Committee of Registering Clinical Trials will be notified.

### Monitoring and publications

The entire progression of the trial and the confidentiality of the data will be monitored by the China Clinical Trial Registration that operates independently from trial researchers and has no competing interests. Any modifications and corrections to operation procedures will be monitored and submitted to the directors of the China Clinical Trial Registration. The findings of the study will be disseminated in academic journals and conference presentations.

